### Sample size

Using a stepped-wedge cluster-randomised trial with eight general internal medicine units, over five time periods or steps (i.e. baseline plus four intervention steps), a sample size of 80 patients per general internal medicine unit (640 patients total) will be sufficient to detect a clinically important decrease in the proportion of patients with a length of stay greater than the median length of stay from 36% to 20%, assuming an intra-cluster correlation of 0.01, with 75% power and a 5% significance level [42]. This will also be sufficient to estimate absolute and relative reductions in mean length of stay between the intervention and control periods.

Western Health’s 2014–2015 admission data showed that the total number of annual separations with an ICD-10 diagnosis code of pneumonia (J12–J18, excluding J35) admitted to a general internal medicine unit at either Footscray or Sunshine Hospital was 1008. It is therefore expected that there will be an adequate number of admissions during the 50-week study period to satisfy the sample size requirements, allowing for an exclusion rate of 20%.

### Data management

All data will be collected through existing routine processes and captured in the patient electronic medical record stored on the password-protected hospital admission information systems (iPM / EDIS v.EDISAPAC 15.1.0 [CSC, Tysons, Virginia USA] and Bossnet [Core Medical Solutions, Rose Park, South Australia]). Data from the electronic medical record will be extracted by study investigators where required throughout admission and after discharge from hospital.

Data will be extracted from iPM and EDIS systems after the patient has been discharged and then separately entered into a dedicated REDCap (research electronic data capture) database [43] hosted at the University of Melbourne, Melbourne, Australia. An investigator will randomly audit data collection of one patient per each ten recruited to ensure data quality and data entry will be randomly checked and cleaned by an investigator, either a chief investigator or an investigator supervised by a chief investigator. On publication of the trial, the database will be made available for independent analysis pending the necessary ethical approvals if requested.

### Statistical methods

In a stepped-wedge design clusters contribute different amounts of time to the intervention and control periods, making traditional measures of covariate balance between intervention arms difficult to use [44]. In this study, we will use a method to assess covariate balance by calculating a weighted average of each baseline characteristic for control and intervention periods; cluster [16] characteristics will be weighted by the amount of person-time they contributed to control and intervention periods (i.e., a cluster that crossed over in Step 2 contributed baseline covariates to two control periods (Steps 0–1) and three intervention periods (Steps 2–4)) [45].

Demographic and clinical characteristics of participants in the study will be described using means and standard deviations for continuous variables, and frequencies and percentages for categorical variables.

Primary and secondary analyses will be as randomised using a multi-level, mixed effects generalised linear model. The effect of the intervention and time period will be considered as fixed effects while the effect of treating general internal medicine unit and patient will be considered as random effects. This will include adjustment for block and time period of the design, seasonal variation in the outcomes (based on the previous 2 years of data), age and sex of the patient admissions [28, 30, 31].

We will make every effort to minimise missing outcome data at each wave. We will report the amounts of missing data according to published recommendations [46]. In addition, sensitivity analyses will be conducted to assess the robustness of the missing data assumption made in the primary analysis. A detailed analysis plan will be developed for secondary and sensitivity analyses. Statistical analyses will be carried out using Stata® (StataCorp. College Station, Texas USA).

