### Randomisation and allocation

As previously described (Fig. 1), the institution has four general internal medicine units at each of two sites (Footscray and Sunshine); therefore, a total of eight units constitute the eight separate clusters used in the stepped wedge. Units will be assigned to usual care or intervention (community-acquired pneumonia service). The order of community-acquired pneumonia service intervention rollout will be randomised (two general internal medicine units at a time across eight general internal medicine units). The random allocation sequence will be generated by a statistician not involved with the study, using Stata version 13.1 (StataCorp. 2013. Stata Statistical Software: Release 13. College Station, TX: StataCorp LP).

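### The primary model lets units differ in level but not drift apart over time; a random unit-by-period effect is a cheap safeguard, and 'block' and repeat enrolment should be clarified in the same edit.

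*Protocol article*

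**What the plan says.** The Statistical methods section sets one mixed effects generalised linear model for primary and secondary analyses. On the fixed side, "The effect of the intervention and time period will be considered as fixed effects". On the random side, "the effect of treating general internal medicine unit and patient will be considered as random effects". It continues: "This will include adjustment for block and time period of the design, seasonal variation in the outcomes", followed by age and sex. What it leaves for later is limited: "A detailed analysis plan will be developed for secondary and sensitivity analyses". The primary model is therefore fixed in this section.

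Randomisation and allocation describes a random rollout order, "two general internal medicine units at a time across eight general internal medicine units". It mentions no blocking or stratification, and the term 'block' is not explained anywhere in the article. Sample size assumes "eight general internal medicine units, over five time periods or steps (i.e. baseline plus four intervention steps"), with "a sample size of 80 patients per general internal medicine unit (640 patients total"), a fall from 36% to 20%, a single ICC of 0.01, 75% power and 5% significance. Nothing is said about correlation weakening over time.

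The eligibility and enrolment sections admit every qualifying patient and exclude those in a different trial. They do not say whether the same person can be enrolled again at a later admission.

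**The concern.** In a stepped wedge the intervention effect comes partly from comparing each unit with itself before and after crossover. Fixed period effects remove drift that all units share. They do not remove drift peculiar to one unit, such as a change of staff or of ward load. With only a unit intercept, that variation is treated as independent patient noise. It is shared by all patients in a unit and period, so the standard error comes out too small and the test rejects too often.

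Two other terms in the same sentences are unclear. Depending on what 'block' means, adjusting for it is either harmless or costs real power. The patient effect has a purpose only if some patients contribute more than one stay. For a patient with one stay it cannot be separated from the residual in a linear model.

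**Working it through.** **Inputs from the protocol (Sample size; Randomisation and allocation).** I = 8 units, T = 5 periods, two units crossing at each of four steps, 640 patients, 36% to 20% (difference 0.16), ICC 0.01, 5% significance. **Assumed.** Two-sided test; equal cells of 640/(8 × 5) = 16; cluster autocorrelation (CAC, the between-period correlation within a unit divided by the within-period one) of 1, 0.8 or 0.5.

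**Step 1: the plan's own power.** For a random unit intercept and fixed periods,

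Var = Iσ²(σ² + Tτ²) / [(IU − W)σ² + (U² + ITU − TW − IV)τ²].

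Here U = 20 is the number of treated cells, W = 2² + 4² + 6² + 8² = 120, and V = 2(4² + 3² + 2² + 1²) = 60. So IU − W = 40 and the τ² multiplier is 400 + 800 − 600 − 480 = 120.

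With pooled variance 0.28 × 0.72 = 0.2016, σ² = 0.99 × 0.2016/16 = 0.012474 and τ² = 0.01 × 0.2016 = 0.002016.

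Var = 8 × 0.012474 × 0.022554 / (0.49896 + 0.24192) = 0.003038, so SE = 0.0551. Power = Φ(0.16/0.0551 − 1.96) = 82.7%.

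Control-rate variance (0.36 × 0.64) gives SE 0.0589 and 77.5%. With a t reference on 34 degrees of freedom, control-rate variance gives 75.1%. The stated 75% is not reproduced exactly by a z test, but it is plausible and, if anything, conservative.

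**Step 2: type I error of the stated cluster structure.** Null data were simulated with normal outcomes and 16 patients per cell, then fitted with a unit intercept and fixed periods and tested against 1.96 (8,000 runs per setting by ML and by REML). The last column adds a unit-by-period effect (REML, 3,000 runs). Monte Carlo error at a 6% rate is √(0.06 × 0.94/8,000) = 0.3 points, and 0.4 points at 3,000 runs.

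| ICC | CAC | Unit intercept only (ML and REML) | With unit-by-period effect |
|---|---|---|---|
| 0.01 | 1 | 6.0–6.3% | 5.7% |
| 0.01 | 0.8 | 6.1–7.0% | 5.1% |
| 0.01 | 0.5 | 6.1–6.7% | 5.8% |
| 0.02 | 0.8 | 7.1–8.1% | 6.3% |
| 0.02 | 0.5 | 7.5–8.1% | 5.9% |
| 0.05 | 1 | 5.9–6.4% | 5.4% |
| 0.05 | 0.8 | 8.1–8.8% | 5.7% |
| 0.05 | 0.5 | 10.1–10.9% | 5.9% |

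At ICC 0.01 the rate is about 6% even with no drift (CAC 1). Most of that excess comes from using a normal reference with eight units, not from the missing term. At ICC 0.05 the missing term is the main cause.

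**Step 3: power with the unit-by-period effect.** In the Step 1 formula put σ² = [(1 − ICC)/16 + ICC(1 − CAC)] × 0.2016 and τ² = ICC × CAC × 0.2016.

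- ICC 0.01: 82.6% at CAC 0.8 and 82.9% at CAC 0.5, against 82.7% without.
- ICC 0.05, CAC 0.8: σ² = 0.013986 and τ² = 0.008064, so Var = 8 × 0.013986 × 0.054306 / (0.55944 + 0.96768) = 0.003979. SE = 0.0631 and power = 71.8%, against 76.7% with CAC 1.
- ICC 0.05, CAC 0.5: 66.8%.

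**Step 4: what 'block' could mean (ICC 0.01, 640 patients, no unit-by-period variation).**

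- Hospital site, balanced across steps: SE 0.0551, power 82.7%, unchanged.
- The pair of units crossing together, as fixed effects: SE 0.0645, power Φ(0.16/0.0645 − 1.96) = 69.9%. With control-rate variance, SE 0.0689 and 64.1%.

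**The case against.** The case against is substantial, and much of it stands.

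- A unit intercept with fixed periods is a recognised stepped-wedge model. It matches the single ICC in the sample size, and period and seasonal terms absorb shared drift. At ICC 0.01 the harm is slight. The 8–11% figures need an ICC five times the protocol's and an autocorrelation found nowhere in the documents. This stands.
- A reader might infer that the primary p-value will be too optimistic because there are only eight units. The article does not say which reference distribution it will use. With t on 6 degrees of freedom the same model gives 1.8–4.5%, so even the direction of the error depends on a choice that is not stated. Such methods are commonly left to an SAP, and their absence here is no fault.
- A reader might infer that the patient effect is a misfit. The documents do not support that. Repeat enrolment is not barred, the model refers to admissions, and for repeat stays the term is legitimate. For single stays in a linear model it is redundant and does not by itself bias the treatment test.
- A reader might infer that adjusting for 'block' leaves the trial under-powered. That holds on one reading only. Moreover, 640 is a minimum: 1008 separations × 0.8 × 50/52 is about 775 patients, and at 775 the crossover-pair reading gives 77.9% (pooled variance) or 72.4% (control-rate), close to the stated 75%.

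What remains is that the primary model is fixed in this section, with no allowance for unit-specific drift and with one term that cannot be interpreted from the article.

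**Conclusion.** The point holds as an inexpensive improvement to the primary model, not as a demonstration that the model fails to fit the design. With a large-sample test, type I error is about 6–7% at ICC 0.01, little of which is due to the omitted term. It is about 8–11% if the ICC were 0.05 with autocorrelation 0.8 to 0.5. Those last values are assumptions, and the simulations use normal outcomes and equal cells, whereas length of stay is typically skewed and recruitment will vary by unit.

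The meaning of 'block' moves power at 640 patients from 82.7% to 69.9% with pooled variance, or from 77.5% to 64.1% with control-rate variance. It therefore needs a definition. Whether patients can re-enter is a matter of clarification, with no bias shown.

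**What to change.** In Statistical methods:

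1. Add a random unit-by-period effect beside the random unit intercept in the primary model. Cost: no material power at ICC 0.01. If the variation is real, intervals widen (for example 76.7% to 71.8% power at ICC 0.05, CAC 0.8). If its variance is estimated as zero, the model returns to the present one.
2. State what 'block' means. If it is hospital site, say so. It should not be fitted as fixed effects for the crossover pair unless the power is restated.
3. State whether a patient may be enrolled more than once, and keep the patient random effect only if so.

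A small-sample correction is advisable but may be placed in the SAP. Its cost is not trivial: with t on 6 degrees of freedom, power at ICC 0.01 is about 68% (pooled variance). The three edits are wording changes to be made before the outcome data are analysed.

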### Trial setting

The two participating hospitals (Footscray Hospital and Sunshine Hospital) are both part of Western Health, a health service that services a population of approximately 700,000 in inner metropolitan Melbourne, Victoria, Australia. Footscray and Sunshine Hospitals are tertiary metropolitan primary referral hospitals with 260 and 510 beds, respectively. Both are publicly funded, university-affiliated teaching hospitals. General internal medicine services manage the largest proportion of patients with community-acquired pneumonia in our health service, with 47% of admissions for community-acquired pneumonia managed by general internal medicine from 2012 to 2013 (average age, 75 years, with proportions with at least 1, 2 or 3 active comorbidities of 70%, 43% and 27% respectively). Western Health has a total of eight general internal medicine units split evenly across the two participating hospitals, which will constitute the eight separate clusters used in the stepped-wedge design.

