#### Intervention 2 – Early switch to oral antibiotics

Guideline-consistent prescription of initial antibiotic therapy and constrained parenteral antibiotic duration (using pre-defined stopping rules) will be provided in the best-practice group [17, 18].

Current institutional general internal medicine antibiotic prescribing practice aims to follow an institutional guideline based on the Australian Antibiotic Guidelines [38]. Patients are stratified as having mild, moderate or severe disease using standardised pneumonia severity criteria. Our institution uses the CORB score, based on its ease and feasibility of use, and it having the highest predictive value for poor outcomes [10]. Based on CORB, most inpatients receive either intravenous penicillin and doxycycline, or roxithromycin (mild or moderate disease), or ceftriaxone and azithromycin (severe disease).

Patients will be switched from intravenous to oral therapy according to the specific criteria for clinical improvement, which will be assessed on a daily basis by the community-acquired pneumonia service using a standardised checklist (also commonly referred to as ‘stopping rules’, see Additional file 2). Essentially, for switching to oral antibiotics, patients must be able to maintain oral intake, have stable vital signs, stable SpO_2_ and no evidence of septic metastases or major exacerbated comorbidities [18].

Any reason for alternative antibiotic selection (such as allergy or advice from an infectious diseases consultant) will be noted.

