### Data collection (see Fig. 4)

#### At enrolment (baseline measures)

Demographic and clinical characteristics will be recorded by collection of the following variables (directly from the patient or the medical record): site, patient age and sex, admitting medical unit, eligibility criteria (age, chest X-ray findings, cough, dyspnoea, temperature, chest auscultation findings, peripheral blood leucocyte count), vital signs on admission (temperature, heart rate, blood pressure, respiratory rate, pulse rate, confusion), estimated glomerular filtration rate, residential care status (independent living, supported accommodation, aged care facility), pre-morbid mobility, function and exercise tolerance, CORB score (derived from confusion, oxygenation, respiratory rate and blood pressure), any relevant comorbidities (e.g. diabetes, immunosuppression, adrenal insufficiency, chronic obstructive pulmonary disease, chronic cardiac failure, malignant process), number of routine medications used by the patient, baseline corticosteroid dose (if any), baseline insulin usage, relevant drug allergies, enrolment in a concurrent inpatient research trial, any decision to initiate palliative care on admission, any adverse events or complications that occur prior to enrolment.

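### The primary model names age and sex as its only patient-level covariates and leaves out the CORB severity, comorbidity and residential care status recorded at enrolment

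*Protocol article*

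**What the plan says.** The protocol article, under Statistical methods, gives a single multi-level generalised linear model for primary and secondary analyses. Intervention and time period are fixed effects; treating unit and patient are random effects. The model also adjusts for block, time period, and "seasonal variation in the outcomes (based on the previous 2 years of data), age and sex of the patient admissions". The same section plans a weighted comparison of baseline characteristics between control and intervention periods, but ties no adjustment to it. The later detailed analysis plan is announced for secondary and sensitivity analyses, so the primary covariate set is the one stated here.

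The enrolment data (At enrolment, baseline measures) include site, residential care status, pre-morbid mobility and "CORB score (derived from confusion, oxygenation, respiratory rate and blood pressure), any relevant comorbidities". None of these is named in the model. A Charlson grouping also exists, but it is derived from ICD-10 discharge coding (At discharge).

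The article itself treats some of these variables as prognostic. Under Intervention 2 it justifies CORB partly by "it having the highest predictive value for poor outcomes". The Background links the elderly, multimorbid group to longer hospitalisation. Trial setting reports 70%, 43% and 27% of patients with at least 1, 2 or 3 active comorbidities.

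**The concern.** Length of stay varies widely between patients, and the trial collects several variables that plausibly explain part of that variation. Leaving them out keeps the residual variance larger than it need be, in a design planned "with 75% power and a 5% significance level".

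The second issue is case mix. Registrars, including the treating registrar, judge eligibility, and the treating consultant decides unclear cases (Ascertainment, enrolment and waiver of consent). Clinicians are not blinded (Blinding). Patients can also be withdrawn after enrolment on consultant review or on transfer within 48 hours (Withdrawal from trial). The mix of enrolled patients may therefore shift when a unit starts the intervention. A unit effect cannot absorb a change that coincides with crossover within the unit, and age and sex would capture only part of it.

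**Working it through.** **Inputs from the article (Sample size; Randomisation and allocation)**
- 8 units, 5 periods, two units crossing at each of four steps.
- 80 patients per unit, 640 in total, so 16 per unit-period.
- Proportion with a long stay 36% versus 20%; difference d = 0.16, mean proportion 0.28.
- Clustering: "assuming an intra-cluster correlation of 0.01".
- 5% significance; two-sided is assumed, as sidedness is not stated.

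**Step 1: reproduce the stated 75%.** The Hussey-Hughes variance is

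Var = I·s²·(s² + T·τ²) / [(I·U − W)·s² + (U² + I·T·U − T·W − I·V)·τ²]

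with I = 8 and T = 5. For this layout U = 20, W = 120 and V = 60, so I·U − W = 40 and the second bracket is 400 + 800 − 600 − 480 = 120.

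Total variance is 0.28 × 0.72 = 0.2016. Hence τ² = 0.01 × 0.2016 = 0.002016, and the within-unit variance is 0.99 × 0.2016 = 0.199584.

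- *All 640 analysed (16 per unit-period):* s² = 0.012474, SE = 0.0551, power = Φ(0.16/0.0551 − 1.96) = 82.7%.
- *20% excluded (512 analysed, 12.8 per unit-period):* s² = 0.0155925, Var = 8 × 0.0155925 × 0.0256725 / (0.6237 + 0.24192) = 0.003700, SE = 0.0608, power = Φ(2.631 − 1.96) = 74.9%.

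The stated figure is reproduced if the article's 20% exclusion allowance is applied to the 640. The article does not say that this was done. Control-arm variance with all 640 and a t reference on 26 to 34 degrees of freedom also gives 74.4% to 75.1%.

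**Step 2: add prognostic covariates.** Let R² be the share of variance explained beyond the terms already in the model. The article gives no value, so a range is assumed. Scaling both variance components by (1 − R²) gives

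power = Φ(2.631/√(1 − R²) − 1.96)

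| Assumed incremental R² | Power from 74.9% base (512) | Power from 82.7% base (640) |
|---|---|---|
| 0.02 | 75.7% | 83.5% |
| 0.05 | 77.0% | 84.6% |
| 0.10 | 79.2% | 86.4% |
| 0.20 | 83.7% | 90.1% |
| 0.30 | 88.2% | 93.4% |

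If only the within-unit variance shrinks, the gain is slightly smaller: at R² = 0.10 with 640 analysed, 86.0% instead of 86.4%.

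**Step 3: would a hospital term help?** With 640 analysed and the correlation held at 0.01, power stays at 82.7% if each step takes one unit from each hospital. It falls to 72.9% if all of one hospital's units cross first. A hospital term therefore gains nothing here and may cost power.

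**The case against.** The strongest reply is that a short prespecified covariate set is a legitimate choice and the article misstates nothing. Several parts of this reply stand.

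- A reader might infer that the model adjusts for age and sex and nothing else. It does not: block, period, season and a unit effect are all there. They largely absorb stable differences between units and changes over calendar time.
- A reader might infer that hospital has been wrongly left out. The eight units are "split evenly across the two participating hospitals", so the unit effect already carries stable hospital differences. Block is undefined and may itself mean hospital, and Step 3 shows no gain from a further term.
- A reader might infer that case mix will differ and will bias the estimate. The article does not show this. It requires identical ascertainment in both conditions, and the Discussion says patients reach units by day of admission or previous admitting unit. What remains is possible case mix that changes with crossover.
- CORB is credited with predicting poor outcomes, not length of stay, and no R² or standard deviation is given.
- The enrolment variables are themselves recorded after unit allocation in a trial with unblinded clinicians. The comorbidity list is open-ended, and no scale is stated for pre-morbid mobility.

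One might add that the adjustment list is not worded as closed and that an analysis plan could extend it. That carries little weight, because the article reserves the later plan for secondary and sensitivity analyses. None of these points removes the core: prognostic variables already collected are not used in the stated primary model.

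**Conclusion.** The point holds as a matter of efficiency and robustness. The stated primary model forgoes precision that data already collected could supply, and some protection against case mix that changes within a unit at crossover. It does not make the planned analysis invalid, and the documents do not support a claim that the estimate will be biased.

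The size cannot be derived from the article. Under an assumed incremental R² of 0.02, 0.10 or 0.20, power rises from about 75% to about 76%, 79% or 84%, that is, by about 1, 4 or 9 percentage points. This rests on a linear variance-reduction formula, a two-sided test and the 512-analysed reading of the stated power. It is illustrative, because the 75% refers to dichotomised length of stay while the primary outcome is length of stay itself. The change should be made because it is cheap, not because the loss is known to be large.

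**What to change.** Before the data are analysed, prespecify these as fixed covariates in the primary model:
- CORB score;
- residential care status;
- a fixed list, or a count, of the comorbidities recorded at enrolment;
- age as a continuous term, with sex and the existing design terms kept.

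Use the enrolment comorbidities and not the Charlson grouping, since discharge coding follows allocation and may depend on length of stay. Include pre-morbid mobility only if it is recorded on a defined scale in the same way in both conditions. Keep the age-and-sex model as a sensitivity analysis. State what block means, and do not add a separate hospital term.

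The cost is a sentence or two in the analysis plan and no new data collection. There are two small downsides. Missing covariate values need a stated rule so that patients are not dropped. Covariates recorded by unblinded staff after allocation will only partly remove any differential case mix.
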